### Health Coaching to Improve Self-Regulation

This study will also test the impact of a coaching intervention focused on enhancing motivation and teaching problem-solving skills to promote long-term outcomes. There is evidence that motivational interviewing and instruction in problem-solving skills can improve medical adherence including in T1D [28-35]. Health coaches will teach these skills in brief web-based sessions in the context of device data review focused on actionable self-management targets. The curriculum begins with motivational exercises to guide selection of concerns that become the target of the problem-solving sessions. The health coach also facilitates engagement with self-monitoring and goal-setting habits using the Glooko data visualization platform and the SweetGoals app goal feedback, consistent with the supportive accountability model [36]. Providing such support increases the efficacy of digital interventions [37-42], and delivery by bachelor’s level coaches can be as effective as professional clinicians across diverse clinical targets [43,44]. The supportive accountability model emphasizes the key role that social presence (human coach) plays in setting clear expectations regarding adherence to the steps necessary to achieve a positive outcome (eg, glucose monitoring) and in supporting goal attainment via progress monitoring and feedback [36]. Our pilot results strongly support the long-term sustained efficacy of this coaching approach combined with incentives [21], but those results cannot inform the need for both of these distinct interventions. This new study will replicate those earlier results in a novel population of young adults and test the separate impact of incentives, coaching, and their interaction.

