Each component will take on 2 levels: yes or no. Note that the factorial design in Table 1 is not a 4-arm trial with each condition compared with a control or to each other. Instead, our interest is in tests of standard analysis of variance main effects and interactions [49]. These involve comparison of outcome means across multiple experimental conditions. For example, the main effect of the incentives component will be tested by comparing the mean of the outcome variable across the 2 conditions in which incentives will be delivered (ie, those in conditions 3 and 4; n=150 before attrition) versus the 2 conditions in which incentives will not be delivered (ie, those in conditions 1 and 2; n=150 before attrition). Hence, this main effect will be tested by comparing half of the sample (those offered incentives) versus the other half (those not offered incentives) in terms of the primary outcome. In this factorial experiment, each effect (including the interaction between the 2 components) will be estimated based on data from all 4 conditions (ie, the full sample) [48,50,51].

Figure 3 shows the study design. An online minimization program (MinimPy) will be used to assign participants [52]. Minimization assures similarity across intervention groups on multiple key covariates [52]. Differences between conditions will be minimized on gender, age, ethnicity (minority vs White), CSII versus MDI, CGM use, and HbA_1c_. Follow-ups will occur at 6 months and 12 months. Compensation will be $25 for the baseline assessment, $50 for each follow-up assessment, and a supplement of $50 for completing both follow-ups. This study was approved by the Committee for the Protection of Human Subjects at Dartmouth College and is registered at ClinicalTrials.gov [NCT04646473].

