#### Implementation, Satisfaction, and App Metrics

For participants who receive human coaching, satisfaction with the human health coach will be assessed at the beginning, during, and the end of the program with the Session Alliance Inventory (α=.94) [86] and an adaption of the Working Alliance Inventory [87,88]. Satisfaction with the SweetGoals digital coach will be assessed at the beginning, during, and at the end of the program with the Session Alliance Inventory [86] and (at the end of the 6-month intervention period only) an adaption of the Working Alliance Inventory [87,88]. We will assess usability of the app components with items from the Usefulness, Satisfaction, and Ease of Use questionnaire (α=.98) [89] and overall app satisfaction with items adapted from Wixom & Todd [90] 3 times (early, midway, and at the end of the 6-month intervention period). In addition, the app will collect engagement metrics including the percentage of messages from digital coaches responded to within 24 hours of receipt and the mean length of the delay between when messages are sent by the app and accessed by the participant. These data will be used to explore objective app engagement and whether satisfaction and app engagement were better when receiving incentives or coaching.

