#### Primary Outcome Analyses

The primary aim is to test the main effects of incentives and coaching on HbA_1c_. We will also test the interaction between components (eg, the synergistic effect of adding one component to another). Two effect-coded indicators (see Collins [51] for detailed justification for using effect coding in the analysis of data from factorial designs) will be created, one for each component: the indicator for incentives (yes vs no) will differentiate between those offered incentives (coded +1; conditions 3 and 4 in Table 1) and those who were not (coded –1; conditions 1 and 2 in Table 1); the indicator for coaching (yes vs no) will differentiate between those offered coaching (coded +1; conditions 2 and 4 in Table 1) and those who were not (coded –1; conditions 1 and 3 in Table 1). To assess the impact of each component on HbA_1c_ over time (baseline, 6 months after, and 12 months after), an LMM will be fit. The model will include fixed effects for time, two component indicators, the component × component interaction, two component × time interactions, and the component × component × time interaction as fixed effects. The LMM will also include random effects for the intercept and time to account for within-person correlation. Based on this LMM, we will test the hypothesis that the yes level of each component (vs no) results in lower HbA_1c_ over time via the component × time interaction parameters.

We calculated the power for testing effects on HbA_1c_ based on the following assumptions: (1) models will include baseline HbA_1c_; (2) a within-person correlation between baseline HbA_1c_ and HbA_1c_ at each follow-up assessment of 0.6 (based on our pilot study); and (3) a standard deviation for HbA_1c_ of 1.2, based on our pilot data. Table 3 shows detectable main effects and interactions in terms of Cohen *d* [92] and HbA_1c_ mean differences. Given n=240 to n=270 (based on 80% to 90% retention), we will be able to detect small effect sizes (Cohen *d*=0.27 to *d*=0.29) with 80% power.

**Table 3 table3:** Aim 1 power for main effects and interaction between components.

Retention %	N	Power %	2-sided *P* value	Cohen *d*	HbA_1c_ difference %
90	270	80	.05	0.27	0.32
85	255	80	.05	0.28	0.33
80	240	80	.05	0.29	0.35

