#### Exploratory Analyses

Informed by the approach of Yardley et al [95], these analyses aim to determine whether app engagement and use metrics predict improvements on HbA_1c_ outcomes. We will first examine how engagement metrics differ between those receiving incentives versus no incentives and coaching versus no coaching. Use metrics will include the percentage of messages responded to within 24 hours of receipt and the mean length of the delay between when messages are sent and accessed. In LMM models predicting HbA_1c_, we will adjust for one or both components if we find significant component effects on engagement metrics. Effects of engagement metrics on HbA_1c_ outcomes are of interest in terms of future refinement and development of the SweetGoals app, suggesting critical app features that may be important to retain in future interventions or features that appear to have less impact and may need to be improved upon in future research [95].

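### The exploratory engagement models adjust for incentives and coaching only after a significant pre-test, so a plausible common cause can be left out; the bias is modest and cheap to remove

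*Protocol article*

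**What the plan says.** The Exploratory Analyses section of the protocol article states its purpose as follows: "these analyses aim to determine whether app engagement and use metrics predict improvements on" HbA1c. Two metrics are named: the percentage of messages answered within 24 hours, and the mean delay before a message is opened.

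The procedure has two steps. First: "We will first examine how engagement metrics differ between those receiving incentives versus no incentives and coaching versus no coaching". Then, in the mixed models for HbA1c: "we will adjust for one or both components if we find significant component effects on engagement metrics". Nothing elsewhere in the article keeps the components in these models when that test is not significant.

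Three other places bear on whether the components could drive both engagement and HbA1c:

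- Primary Outcome Analyses: "The primary aim is to test the main effects of incentives and coaching on" HbA1c.
- Health Coaching to Improve Self-Regulation: "The health coach also facilitates engagement with self-monitoring and goal-setting habits using the Glooko data visualization platform and the SweetGoals app goal feedback".
- Implementation, Satisfaction, and App Metrics: the engagement data will be used to explore "whether satisfaction and app engagement were better when receiving incentives or coaching".

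The Secondary Outcome Analyses section deals with a similar question, the effect of a post-randomization mediator on HbA1c. There, each component and their interaction are in the model with no pre-test.

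**The concern.** A factor that affects both engagement and HbA1c confounds the association between them. Here the candidate factors are the two randomized components, which are measured without error and are free to include. The rule lets a P value on the engagement side decide whether they enter. A non-significant result does not show that a component has no effect on engagement. At this sample size, small effects are missed often.

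If the components work as hypothesized, the error has a fixed direction: part of the benefit of coaching or incentives is credited to app use. If the rule is applied metric by metric, one metric may also be adjusted and the other not, by chance, and their coefficients would not be comparable. The section says the results may inform which app features to retain or improve, and that is where such an error would be felt.

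**Working it through.** **Inputs from the article**

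- Retained sample: "Given n=240 to n=270 (based on 80% to 90% retention"). I use N of about 250.
- Equal split on each factor, for incentives: "those in conditions 3 and 4; n=150 before attrition" against the other 150.
- HbA1c SD 1.2 and baseline to follow-up correlation 0.6 (Primary Outcome Analyses). The baseline-adjusted residual SD is 1.2 × √(1 − 0.6²) = 0.96.
- Component effect on HbA1c: 0.32% (Table 3, 90% retention). As an upper value, 0.45 × 1.2 = 0.54%, from the d of 0.45 in the prior adolescent trial. That d belongs to the combined intervention, so it is generous for one component.

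**Assumed, because the article gives no figure**

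- Component effect on engagement: 0.25 SD each, with a range of 0.1 to 0.5. Engagement is coded so that higher means more use.
- Two-sided alpha 0.05 for the pre-test, additive component effects, and a true engagement slope of zero.
- One baseline-adjusted follow-up, as a simplification of the mixed model.

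**Step 1. Reproduce the plan's own power figure.** Table 3: d = (1.960 + 0.842) × √(4/N) × √(1 − 0.36). This gives 0.273, 0.281 and 0.289 for N = 270, 255 and 240, against the stated 0.27, 0.28 and 0.29. It reproduces. No power is given for the engagement pre-test.

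**Step 2. How often the pre-test misses.** At N = 250 the noncentrality is 0.25 × √250 / 2 = 1.98, so power is about 51% and the miss rate about 49% per component. Both are missed in about 0.49² = 24% of trials, and at least one in about 1 − 0.51² = 74%. Miss rate per component by true engagement effect:

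| N | 0.1 SD | 0.2 SD | 0.25 SD | 0.3 SD | 0.4 SD | 0.5 SD |
|---|---|---|---|---|---|---|
| 300 | 86% | 59% | 42% | 26% | 7% | 1% |
| 240 | 88% | 66% | 51% | 36% | 13% | 3% |

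**Step 3. Bias if both components were never adjusted for.** Slope = −2 × 0.32 × 0.25 × 0.25 / (1 + 2 × 0.25²/4) = −0.039% HbA1c per SD of engagement. This is a reference point and not the planned rule.

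**Step 4. Why the planned rule does less harm.** A component is omitted only when its observed difference in engagement is below about 1.96 × √(4/250) = 0.248 SD. The omitted-component bias in such a trial is therefore at most about 0.32 × 0.248 × 0.25 / (1 + 0.248²/4) = 0.020% for one component, and about twice that for both.

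**Step 5. Simulation of the rule** (N about 250, 0.25 SD on engagement for both components, rounded over repeated runs):

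| Analysis | Bias, 0.32% effects | Type I error | Bias, 0.54% effects | Type I error |
|---|---|---|---|---|
| Planned rule, all trials | −0.012 | about 5.5% | −0.02 | about 6% |
| Planned rule, both missed (24% of trials) | about −0.025 | 6 to 7% | −0.04 | about 8.5 to 9% |
| Always adjust | 0.00 | about 5% | 0.00 | about 5% |
| Never adjust (not planned) | −0.039 | about 9.6% | – | – |

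**Step 6. Sensitivity.** Among the engagement effects simulated (0 to 0.4 SD in steps of 0.1), the average bias under the rule is largest at 0.2 SD. At N = 240 with d = 0.29 on HbA1c, it is −0.0123 × 1.2 = −0.015% per SD, with type I error 6.0%. At an engagement effect of 0.4 SD it falls to −0.0026 × 1.2 = −0.003%, because the pre-test then usually succeeds. At zero effect there is no bias.

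**The case against.** The strongest reply is that the rule mostly protects itself. It adjusts when the imbalance is visible, and when it does not adjust, the observed imbalance is necessarily small. This stands, and it limits the size of the point. A reader might infer that the false-positive rate doubles from 5% to about 10%. That figure, with its bias of about −0.04% at 0.32% HbA1c effects, belongs to a model that never adjusts for either component. The article does not plan that model.

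Second, the components are not established common causes. Their effects on HbA1c are the hypothesis under test, and their effects on engagement are a question the trial will explore. The text gives some support for coaching. Incentives pay for glucose monitoring and mealtime goals, not for answering messages. If a component moves neither engagement nor HbA1c, or only one of them, leaving it out causes no confounding. This stands too: the right word is plausible, not known.

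Third, the analysis is headed exploratory and its stated use is tentative, so the text does not support saying that it will decide which features are kept. Engagement is not randomized, and confounding by motivation, for example, would remain after any fix.

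None of this is a reason for the pre-test. It gains almost nothing, and the article does without it in the parallel mediation models. Nor is this a detail left to an analysis plan that is not shown: the rule is stated.

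**Conclusion.** The concern holds as a minor point. The article makes adjustment for randomized components depend on a significance test, and this can leave out a plausible common cause and let the adjustment set vary by chance.

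The size is modest. With 0.25 SD engagement effects, the average bias is about −0.01% HbA1c per SD at HbA1c effects of 0.32%, and about −0.02% at 0.54%. Type I error is about 5.5 to 6%. In the quarter of trials where both components are missed, the bias is about −0.025% to −0.04%, and type I error is 6 to 7% at the smaller HbA1c effect and 8.5 to 9% at the larger. These figures rest on assumed engagement effects, additivity and a single-follow-up simplification.

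The primary test of the components on HbA1c and the mediation models are unaffected.

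**What to change.** Replace the conditional sentence with an unconditional one, for example: *All linear mixed models of engagement metrics on HbA1c include both component indicators, with the same component terms as the primary model, regardless of the component–engagement tests.* The comparison of engagement by component can stay as a descriptive result in its own right.

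The defect does not call for adding baseline HbA1c as a covariate; baseline is already one of the outcome time points in the primary model.

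The cost is one sentence and a few degrees of freedom out of roughly 240 to 270 participants. In the simulations, always adjusting brought the bias to about zero and type I error to about 5%.

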## Results

We anticipate recruiting 300 young adults in a 36-month period (approximately 8 per month). The anticipated date of enrollment of the first participant is February 2021. We expect that data collection will be complete by February 2025. We expect to complete analyses of the primary and secondary outcomes by December 2025.

## Discussion

### Design Innovations

This study focuses on investigating the utility of two intervention components, seeking to optimize an intervention for improving glycemic outcomes among young adults with T1D. Innovations include recruiting participants with T1D into an intervention via social media and intervention delivery via an app plus coaching and incentives both delivered remotely, strategies that may be vital to reaching the targeted, understudied, and underserved population of young adults. In addition, this is the first intervention designed to target adherence via incentives among patients using diverse glucose measurement methods (glucometer, CGM) and methods of insulin delivery (MDI, CSII). This trial also makes innovative use of existing diabetes device technology by integrating a diverse array of devices with an app to automate tracking of and feedback on daily adherence habits. This digital and web-based model is designed to be broadly applicable across the range of health conditions in which patients struggle with self-management.

### Design Considerations

The study design was informed by research evidence across multiple domains. For example, the focus on young adults was based on evidence suggesting they are at unique risk for above target HbA_1c_ levels and that periods of above target HbA_1c_ levels during these years have a long-lasting negative impact on health [96]. We chose to focus on early young adulthood (ages 19 to 25 years) due to their higher risk for above target HbA_1c_ [97] and possible developmental differences across the later 20s and early 30s. Further, we chose to target young adults outside the traditional clinic setting directly via social media, empowering them to address their diabetes self-management. Many young adults are less compliant with obtaining regular medical care [98], which suggests it may be important to offer services to young adults with T1D outside the endocrinology setting to problem solve their barriers to clinical care and encourage them to schedule regular visits with their provider. This proposed model focuses on directly engaging participants rather than targeting changes in provider behavior. As such, it offers a practical outreach approach that could be deployed nationally and adopted by medical practices, health systems, or insurers outside of office visits to engage young adults with T1D in working together with their provider and managing their own health.

#### Intervention Targets

There were several decisions made in relation to our choice of particular adherence behaviors to target. Key to effectively using incentives to change behavior is the identification of specific, objectively verifiable, targets. Research on diabetes has long identified self-monitored blood glucose (SMBG) as a fundamental adherence behavior related to better glycemic control [99], and our pilot research focused on increasing SMBG. However, the increasing use of CGM (approximately 25% in the T1D Exchange sample [97]) led us to develop a strategy to include all participants with above target HbA_1c_, using any combination of diabetes devices. This choice required us to identify a key adherence behavior necessary for CGM use to have a positive impact on glycemic control. Research suggests that CGM wear time is the analog to SMBG that positively impacts glycemic control [100]. Of note, high wear time is defined as providing 80% of expected glucose values each day, based on a review of CGM studies and the recent international consensus statement [101]. By selecting targets that allow the inclusion of participants using all current glucose monitoring devices, we have greatly increased the intervention generalizability.

There are many other self-management behaviors in addition to glucose monitoring necessary to achieve below target HbA_1c_ levels, and these primarily reflect timely and accurate insulin dosing. In selecting additional specific, objectively verifiable targets related to insulin dosing we needed to address multiple challenges. Some of these include the different regimens and rules associated with use of MDI versus CSII, highly individualized insulin dosing regimens across participants, and diverse circumstances under which the dosing rules should be altered (eg, when ill, due to exercise, due to nutritional factors other than simply the number of carbs consumed). It is also not possible to objectively verify for a patient who uses MDI the timing and amount of insulin delivered. For these reasons, we opted to focus on mealtime behaviors involving a glucose value less than 30 minutes prior to an entered carb value, a pair of behaviors that are fundamental to accurate insulin dosing and that are required of all participants regardless of method of insulin dosing.

Ideally, mealtime adherence reflects 3 steps: a properly timed glucose check, entry of the number of carbs consumed, and correct insulin dosing. There are few data regarding carb counting among young adults who do not use CSII. However, research has investigated adherence among young adults using CSII [56,102-106]. Overall, adherence is highly variable across individuals, and days on which a mealtime bolus occurs more than 3 times are significantly correlated with HbA_1c_ [103,105,107,108]. Participants who complete these first two steps (glucose check and carb entry) are likely to deliver a bolus, as supported by research showing that the sequence of a properly timed glucose check and a carb entry without a bolus occurred less than 1% of the time [56].

In selecting adherence targets, we also considered targeting individual glucose levels or time in the target glucose range. Unfortunately, for participants who do not use CGM, these data are sparse and potentially not representative of daily fluctuation in glucose levels. Our selected mealtime behaviors are more actionable and are key adherence behaviors for participants using CGM, even when hybrid closed-loop systems are in widespread use [109-114]. Further, access to such systems is often allowed only for participants showing adherence and moderate HbA_1c_ elevations. For example, in the recent closed-loop study with patients with above target HbA_1c_ levels, participants with HbA_1c_>10% were excluded and participants were required to show use of CGM for at least 12 days and use of the bolus calculator for at least 75% of meal boluses over 2 weeks prior to randomization [115]. Finally, discontinuation rates for such systems may be high [116], suggesting the continued need for solutions to improve outcomes for participants using diverse treatment regimens.

